#### Superiority

If non-inferiority is conducted for the primary outcome, the superiority of the corresponding comparison will be evaluated for each outcome using an overall *α* of 0.025 with Holm-Bonferroni correction for testing both outcomes (upper limit of 97.5%CI smaller than predefined margin for most significant outcome and upper limit of 95% CI for the other). If superiority is detected on at least either cumulative 24 h opioid consumption or pain NRS scores, the ESPB group will be claimed to be better than TPVB group.

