## Statistical analysis

### Sample size calculation

The primary endpoint of this non-inferiority trial is the joint of cumulative 24 h opioid consumption after surgery and average pain NRS score at 24 h postoperatively.

In a pilot investigation of our patients, the mean (± standard deviation) of the cumulative 24 h opioid (sufentanil) consumption after laparoscopic nephroureterectomy was about 25.7 (± 2.0) μg with TPVB and 35 (± 14.0) μg with non-block respectively (data were unpublished yet). The non-inferiority margin was set as 5 (unit: μg; clinical practice treated it as an acceptable difference) [27]. With a significance level of *α* = 0.05 and a power of 1-β = 90%, the sample size required to detect difference was 77 patients in each group.

A 1–1.3 point difference in pain NRS scores is usually considered as acceptable subjective pain discrimination [28]. When the standard deviation of the pain NRS score was assumed as 2.5 and the non-inferiority margin of NRS was 1 score [29], 70 samples were estimated per group.

Hence, the greater sample calculated above was 77 participants per group. Considering a dropout rate of 5% and technique failure rate of 3%, we finally planned to enroll 83 participants per group (a total of 166 participants). The sample size was estimated by the PASS software (version 11.0; NCSS PASS, UT, USA).

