### Primary endpoint

#### Non-inferiority

Cumulative 24 h opioid consumption and average pain NRS score at 24 h after surgery is the primary joint endpoint, which will be analyzed by “joint hypothesis test.” In this analysis, the intervention group could be considered effective as long as either of the two endpoints is non-inferior. The confidence interval method will be used to perform the non-inferiority test, and the result will be expressed as effect size (difference) (95% CI). If the effect size upper limit of the one-side 95% CI is smaller than 5 in cumulative 24 h opioid consumption, we will conclude that ESPB is non-inferiority to TPVB; in addition, when average pain NRS scores at 24 h after surgery is smaller than 1, ESPB group will be also considered non-inferiority.

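### The superiority step compares the upper confidence limit with a predefined margin, and the only margins defined are for non-inferiority, so as written it cannot show that ESPB is better

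*Protocol article*

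**What the plan says.** Under Primary endpoint, the Superiority section opens a superiority evaluation once non-inferiority has been concluded. It sets an overall alpha "of 0.025 with Holm-Bonferroni correction for testing both outcomes" and gives the criterion in brackets: "upper limit of 97.5%CI smaller than predefined margin for most significant outcome and upper limit of 95% CI for the other". One outcome is enough for the claim: "If superiority is detected on at least either cumulative 24 h opioid consumption or pain NRS scores", ESPB is to be declared the better block.

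The section does not say which margin it means. The article defines two, both in the Sample size calculation section and both as non-inferiority margins. For opioid use, "The non-inferiority margin was set as 5" (μg of sufentanil). For pain, the SD was "assumed as 2.5 and the non-inferiority margin of NRS was 1 score". The Non-inferiority section uses the same values as its limits, for example "If the effect size upper limit of the one-side 95% CI is smaller than 5 in cumulative 24 h opioid consumption". The article states no superiority margin and no comparison with 0.

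**The concern.** For both outcomes a higher value is worse, so the quantity of interest is ESPB minus TPVB, and ESPB is better only if that difference is below 0. An upper limit below +5 μg or +1 point shows that ESPB is not worse by that amount. It is compatible with no difference, and with ESPB being somewhat worse.

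Taken literally, the superiority step is therefore a second non-inferiority test with a stricter interval, reported under the label of superiority. The prior non-inferiority gate gives no protection: an outcome whose 97.5% limit lies below the margin also has its one-sided 95% limit below the same margin. What is at stake is a published statement that ESPB is better than TPVB, with a nominal error rate of 0.025 that does not belong to that statement.

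**Working it through.** **Inputs**

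- Margins: 5 μg and 1 NRS point (Sample size calculation).
- NRS SD: 2.5 (same section).
- n = 77 per arm, the stated number before allowance for dropout and technique failure.
- Opioid SD: an assumption, 10 to 14 μg. The article gives only pilot figures: consumption "was about 25.7 (± 2.0) μg with TPVB and 35 (± 14.0) μg with non-block respectively". The root mean square of these SDs is √((2.0² + 14.0²)/2) = √100 = 10. The larger pilot SD is 14.
- Correlation between the two outcomes: not given; assumed 0 to 0.6.
- Interval: two-sided 97.5%, so z = 2.241 (one-sided 0.0125). For a claim on at least one outcome, only the first Holm step matters.

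**Step 1. Reproduce the plan's alpha with the limit compared with 0.** With equal arms and independent outcomes, the chance that at least one upper limit falls below 0 is 1 − (1 − 0.0125)² = 0.0248. At correlation 0.6 the bivariate normal gives 0.0225. This matches the stated 0.025, so the Holm levels fit a test against 0 with two-sided intervals.

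**Step 2. Each outcome against its margin, equal arms.** SE = SD × √(2/77) = SD × 0.1612, and P(upper limit < margin) = Φ(margin/SE − 2.241).

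| Outcome | SE | margin/SE | P(passes) |
|---|---|---|---|
| Opioid, SD 10 | 1.612 | 3.102 | Φ(0.861) = 0.805 |
| Opioid, SD 14 | 2.256 | 2.216 | Φ(−0.025) = 0.490 |
| NRS, SD 2.5 | 0.403 | 2.482 | Φ(0.241) = 0.595 |

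**Step 3. At least one outcome passes, equal arms.** At correlation 0:

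- SD 10: 1 − (1 − 0.805)(1 − 0.595) = 0.92.
- SD 14: 1 − (1 − 0.490)(1 − 0.595) = 0.79.

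From the bivariate normal at correlation 0.6: 0.85 (SD 10) and 0.69 (SD 14). The range is 69–92%, against 2.2–2.5% in step 1.

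**Step 4. ESPB truly worse by half of each margin (2.5 μg and 0.5 points).** P(passes) = Φ(half-margin/SE − 2.241): 0.245 (opioid, SD 10), 0.129 (opioid, SD 14) and 0.159 (NRS). At least one passes, at correlation 0: 1 − 0.755 × 0.841 = 0.36 (SD 10) and 1 − 0.871 × 0.841 = 0.27 (SD 14). At correlation 0.6: 0.31 and 0.22. The range is 22–36%.

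**Step 5. What data would count as superior.** The largest observed difference that passes is margin − 2.241 × SE. For opioid at SD 10 it is 5 − 3.61 = +1.39 μg, and for NRS it is 1 − 0.903 = +0.10 points. Both are observed results in favour of TPVB. At SD 14 the opioid figure is −0.06 μg, so on that outcome ESPB would need to look marginally better.

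**Sensitivity, equal arms.**

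- If 97.5% is read as one-sided (z = 1.960), the claim rate is 91–96% at SD 10 and 79–88% at SD 14. Against 0 it would then be 4.4–4.9%, above the stated 0.025.
- With 83 per arm and two-sided limits: 88–94% (SD 10) and 73–82% (SD 14).
- At correlation 1 and SD 14 the rate is still about 60%, from the NRS outcome alone.
- With the pilot TPVB SD of 2.0 in both arms the claim would be practically certain.

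**The case against.** The strongest defence is that this is a slip in a bracket. The step has its own heading, follows non-inferiority, and uses 0.025 with Holm. One-sided 0.0125 and then 0.025 correspond to two-sided 97.5% and 95% intervals, the usual construction for superiority against 0. Repeating the non-inferiority test with a wider interval would serve little purpose. This is a plausible account of intent. It does not rescue the text, because the article never mentions 0 and the stated alpha and the stated criterion cannot both hold.

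A second objection is that the size depends on inputs the article does not settle. That stands. An opioid SD of 10.6 μg, for instance, can be back-solved from 77 per arm at one-sided 0.05 and 90% power, but it is not stated. On the opioid outcome alone at SD 14 the false-claim rate is 49%, so a majority of equal trials follows only under the either-outcome rule. A range is the honest way to report it.

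A third objection is scope: the trial's hypothesis is non-inferiority and superiority is a conditional follow-on. That is right, and it confines the point to any claim that ESPB is better.

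A reader might also infer that superiority should open only after non-inferiority on both outcomes. That does not follow from this defect. The Non-inferiority section accepts either outcome as a stated rule, and the Superiority section refers to the corresponding comparison, which can be read as limiting the test to the outcome already shown non-inferior. Requiring both is a separate design question with a power cost: with equal arms at 77 per arm, both outcomes would pass the one-sided 95% test in only about 57–75% of trials (opioid SD 14 to 10.6, correlation 0 to 0.5).

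**Conclusion.** The criterion is wrong as written. A limit below the non-inferiority margin cannot support a claim that ESPB is better, and the overall alpha of 0.025 does not govern that claim. With equal arms the literal rule yields the claim in about 69–92% of trials, against about 2% when the limit is compared with 0; with ESPB worse by half of each margin the rate is about 22–36%. These figures rest on a normal approximation, 77 per arm, NRS SD 2.5, and the assumed opioid SD and correlation. Every either-outcome scenario tried with equal arms gave more than 50%.

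A reader might go further and infer that the investigators mean to call an equal block superior, or that the non-inferiority conclusion and the sample size are undermined. The document supports neither. The Holm levels point towards 0 as the likely intent, and this defect leaves the non-inferiority test and the sample size untouched.

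**What to change.** In the Superiority section, replace the comparison with the predefined margin by a comparison with 0 at both Holm steps. Define the difference as ESPB minus TPVB. Require the upper limit of the two-sided 97.5% CI to be below 0 for the most significant outcome and, if that is met, the upper limit of the two-sided 95% CI to be below 0 for the other. State explicitly that both intervals are two-sided, so that they match the overall alpha of 0.025. Make the change before allocation is revealed for analysis.

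The cost is a wording correction in the protocol, and in the analysis plan if it carries the same text. It changes no sample size, data collection or non-inferiority rule. Whether non-inferiority on both outcomes should come first is not part of this change.

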### Secondary endpoint

For the opioid consumption and pain NRS scores at other different timepoints after surgery, repeated measure ANOVA (analysis of variance) will be performed if normality and homogeneity of variance and sphericity hypothesis (Mauchly’s test) are met. If not, one-way ANOVA and its correction (Greenhouse-Geisser coefficient correction and Huynh-Feldt coefficient correction) as well as generalized estimated equation (GEE) model will be performed. As for inter-group comparison, independent sample *t* test will be used for comparison if the distribution accords normality assumption; if distribution is skewed as well as not independent at different timepoints, the difference will be determined by Mann-Whitney *U* test.

Outcome analyses will be performed in the intention-to-treat (ITT) population, i.e., all patients are analyzed in the group to which they are randomized and received at least part of study intervention. A per-protocol (PP) analysis will be also performed for the primary endpoint. Statistical analysis will be performed by professional biostatisticians. All conclusions will be based on the original data.

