### Endpoints analysis

Baseline characteristic will be compared according the data distribution and type. In addition to graph method for qualitative analysis, Shapiro-Wilk test will be also used for quantitative analysis in review of data distribution. Continuous data with normal or approximate normal distribution will be expressed as mean ± standard deviation, while continuous data with non-normal distribution is expressed as median (interquartile, IQR). Continuous data will be tested by independent sample *t* test or Mann-Whitney *U* test according to data distribution. Categorical data will be expressed as numbers (percentages) and tested by chi-square test/Fisher’s exact test. Time-to-event data will be analyzed by the Kaplan-Meier estimator, with the difference between groups tested by the log-rank method. Two-tailed *p* values of less than 0.05 are regarded as statistically significant. All statistical analyses are performed with the SPSS 25.0 statistical package (IBM SPSS Inc., Chicago, IL, USA).

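### Assumption tests decide whether pain and opioid use over time are analysed by complete-case ANOVA alone or also by an available-data GEE, and no lead analysis is named

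*Protocol article*

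**What the plan says.** All references are to the protocol article.

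- **First choice.** Statistical analysis, Secondary endpoint: "repeated measure ANOVA (analysis of variance) will be performed if normality and homogeneity of variance" hold, together with sphericity by Mauchly's test.
- **Fallback.** The same paragraph continues: "If not, one-way ANOVA and its correction (Greenhouse-Geisser coefficient correction and Huynh-Feldt coefficient correction"), "as well as generalized estimated equation (GEE) model will be performed". The two epsilon corrections belong to repeated-measures ANOVA, so I read the first part as that ANOVA with corrected degrees of freedom. The text does not say which of the two analyses leads.
- **Group comparison.** "As for inter-group comparison, independent sample *t* test will be used for comparison if the distribution accords normality assumption", with Mann-Whitney U otherwise.
- **Population.** Outcome analyses are intention-to-treat: "all patients are analyzed in the group to which they are randomized", provided they received at least part of the intervention.
- **Readings.** Endpoints, Secondary endpoint: 0.5, 2, 6, 18, 24 and 48 h, for cumulative opioid and for NRS.
- **Software and expected loss.** Endpoints analysis: "All statistical analyses are performed with the SPSS 25.0 statistical package". Sample size calculation: "Considering a dropout rate of 5% and technique failure rate of 3"%, giving 83 per group.
- **Data capture.** Data collection and management states the aim of recording every timepoint. The article gives no rule for a missing reading.

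**The concern.** Classical repeated-measures ANOVA works on complete response vectors. In SPSS a patient with one missing reading is removed from all six timepoints. GEE keeps every patient with at least one reading. The two methods can therefore describe different patients, and the planned tests decide which of them are run:

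- If all three assumptions pass, only the complete-case ANOVA is fitted.
- If any fails, a complete-case ANOVA and an available-data GEE stand side by side without a stated order.

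In the second case one secondary endpoint can yield two answers from two patient sets, with the choice between them left open until the data are seen.

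The stake is precision first. Bias is possible if readings are missed more often in patients with more pain. The arm with more pain then loses more of its worst cases, and the contrast between blocks shrinks. In a trial whose hypothesis is similar analgesia, that direction is the uncomfortable one, even for a secondary endpoint.

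**Working it through.** **1. The plan's own figure.** The only stated figure that bears on missing data is the inflation of 77 to 83 per group for 5% dropout plus 3% technique failure. 77 × 1.08 = 83.2 and 77 / 0.92 = 83.7. The stated 83 is reproduced to within one patient, and nothing below depends on that difference.

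**2. Loss at the stated dropout.** If the 5% dropout is the only source of missing readings, complete cases = 166 × 0.95 = 157.7, about 158. Interval widening = 1/√0.95 − 1 = 2.6%. A patient who leaves before any reading is lost to every method, so the ANOVA's extra loss is at most this. Technique failures need not miss readings and are not counted.

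**3. Loss with scattered missing readings.** No rate per reading is given, so the rate p is an assumption. With independent missingness over six readings, share dropped = 1 − (1 − p)^6 and widening = 1/√((1 − p)^6) − 1.

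| p per reading | Share dropped | Complete of 166 | Per group of 83 | Interval wider by |
|---|---|---|---|---|
| 0% | 0% | 166 | 83 | 0% |
| 1% | 5.9% | 156 | 78 | 3% |
| 2% | 11.4% | 147 | 74 | 6% |
| 3% | 16.7% | 138 | 69 | 10% |
| 5% | 26.5% | 122 | 61 | 17% |

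**4. Possible bias.** This was simulated with six visits, SD 2.5 (the article's NRS value), and a true constant difference of 1 point. Assumed: within-patient correlation 0.5, and a chance of missing a reading that rises with the previous score (logit slope 0.5 per NRS point). The baseline missing rate was varied.

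| Complete cases, arm with less vs more pain | Estimated difference (truth 1.0) |
|---|---|
| 93% vs 90% | 0.94 |
| 84% vs 77% | 0.88 |
| 80% vs 72% | 0.86 |
| 77% vs 68% | 0.83 |

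Under these assumptions the bias is modest and always toward no difference. If missingness is unrelated to pain, only precision is lost.

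**5. Which branch will be reached.**
- Cumulative opioid breaks sphericity by construction, because its variance grows with time. With 77 per arm and the six timepoints, Mauchly's test rejected in 100% of simulated runs (epsilon 0.21 to 0.40). This held with independent increments and with 50% or 90% of the 24 h variance shared.
- For an integer NRS with SD 2.5 and n = 77, Shapiro-Wilk rejected in 58% of runs at mean 5 and in almost all at mean 3.

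The fallback is therefore the likely path, and its missing order of precedence matters more in practice than the ANOVA-only branch.

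**6. Which analyses change the patient set.**

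| Planned analysis | Patients used |
|---|---|
| Repeated-measures ANOVA | All six readings present |
| ANOVA with Greenhouse-Geisser or Huynh-Feldt correction | Same complete cases |
| GEE | At least one reading |
| t test or Mann-Whitney U, read as per timepoint | That reading present |

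**The case against.** A reader might infer that the named ANOVA cannot deliver the intention-to-treat analysis. The article does not support that. It holds only if readings are missing and not imputed. The missing-data rule may be in an analysis plan or full protocol that is not shown, and its absence from an article is no fault. Follow-up is short, with readings ending at 48 h and full capture intended. With no missing readings there is no conflict.

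A reader might also infer that Mauchly's test alone decides who is analysed. It does not. Normality and homogeneity of variance are conditions too, and the corrected ANOVA in the fallback uses the same complete cases. Only the added GEE brings other patients in.

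A third tempting inference is that the trial's conclusion is biased toward similarity. Non-inferiority rests on confidence intervals for 24 h opioid use and 24 h NRS, which these time-course analyses do not enter.

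It is also fair to say that the per-timepoint tests already use available data, that the ANOVA-only branch will seldom be reached, and that losses above 5% rest on assumed rates. All of this limits the size of the point. What remains does not rest on an omission: the text itself fixes a complete-case method, makes the available-data model conditional on assumption tests, and leaves two fallback analyses unranked.

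**Conclusion.** The point holds as a weakness of the secondary time-course analyses. The plan makes an all-available-data model depend on tests of normality, homogeneity of variance and sphericity, and does not say which analysis leads once they fail. The cost ranges from nothing with complete data, through about 5% of patients at the stated dropout, to 6% to 27% if 1% to 5% of readings are missing independently. Attenuation of a 1-point difference to between 0.94 and 0.83 needs the further assumption that missingness follows pain. Listwise deletion is a property of the method and software rather than a statement in the article. The change is worth making because it is nearly free. The primary conclusion does not depend on it.

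**What to change.** Before unblinding, name one all-available-data model as the lead analysis of opioid use and NRS over time, in the intention-to-treat population as the article defines it. Two choices are acceptable:

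- a linear mixed model for repeated measures (MIXED in SPSS) with group, categorical time, group-by-time and an unstructured within-patient covariance; or
- the GEE already planned, with robust variance.

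Report ESPB − TPVB differences with 95% CI at each timepoint. Delete the repeated-measures ANOVA, in both its uncorrected and corrected forms, and the assumption-test switch.

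There is a trade-off. The Gaussian mixed model is approximate for skewed opioid use and a bounded NRS, which favours robust GEE. Ordinary GEE, however, relies on missingness unrelated to the outcome, whereas the mixed model tolerates dependence on earlier recorded values.

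The cost is a few lines of text, with the same data, software and patients. Trial status describes enrolment as ongoing, and Blinding releases the allocation only after database lock, so as of the article there is time to make the change.

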#### Secondary endpoint

Cumulative opioid consumption at other different times (0.5 h, 2 h, 6 h, 18 h, 24 h and 48 h) after surgery, as well as the time interval to the first bolus demand in PCIA pump, the numbers of required and administered boluses in PCIA pump.Somatic and visceral pain NRS scores both at rest and with movement at preset timepoints (0.5th h, 2nd h, 6th h, 18th h, 24th h, and 48th h) postoperatively.Besides PCIA pump, demand of other rescue analgesic (observed at preset different timepoints, including the time interval to the first rescued analgesic in PACU or in ward).

The other endpoints are defined as follows:
Clinical features of blockage including time-consumption for the intervention, the onset time and time to fixed sensory block, dermatomal distribution of sensory loss, predefined regional distribution of sensory loss, times of puncture, and the adverse events.Quality of recovery scores (QoR-15) (assessed by QoR-15 questionnaire [22]) face-to-face at 24 h after surgery.Sleep quality scores on the nights of the first 2 days after surgery (assessed with NRS scores, 0 = best sleep quality whereas 10 = worst sleep quality).The incidence of postoperative vomiting and nausea score assessed with NRS scores (0 = no nausea whereas 10 = severe nausea) at the following timepoints (0.5th h, 2nd h, 6th h, 18th h, 24th h, and 48th h) postoperatively.The incidence of postoperative moderate to severe pain.Overall incidence of postoperative complication (observation period: until discharge, classified by Clavien-Dindo Classification) [23].Time to first ambulation and diet (observation from the end of surgery).Length of postoperative hospital stay and total length of hospital stay.Anesthesia cost and total hospitalization cost.

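### The fallback analysis for the repeated secondary outcomes is mis-specified and names no governing analysis

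*Protocol article*

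**What the plan says.** The Protocol article lists two groups of repeated secondary outcomes under Endpoints, Secondary endpoint. The first is "Cumulative opioid consumption at other different times (0.5 h, 2 h, 6 h, 18 h, 24 h and 48 h) after surgery". The second is somatic and visceral pain NRS at rest and with movement, at "0.5th h, 2nd h, 6th h, 18th h, 24th h, and 48th h) postoperatively". Each patient therefore gives six readings per series.

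Statistical analysis, Secondary endpoint, sets out the analysis in three steps:

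- First choice: a repeated-measures ANOVA, provided that the data pass checks of normal distribution, equal variance and, by Mauchly's test, sphericity.
- Fallback when any of these checks fails: "one-way ANOVA and its correction (Greenhouse-Geisser coefficient correction and Huynh-Feldt coefficient correction) as well as generalized estimated equation (GEE) model will be performed".
- Comparison between arms: a t test if the data are normal. Otherwise, "if distribution is skewed as well as not independent at different timepoints, the difference will be determined by Mann-Whitney".

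Under Endpoints analysis, two-tailed p "values of less than 0.05 are regarded as statistically significant". The paragraph on secondary endpoints gives no order of precedence among these analyses and no multiplicity rule.

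**The concern.** The fallback names a combination that does not exist. Greenhouse-Geisser and Huynh-Feldt adjust the degrees of freedom of within-subject F tests in a repeated-measures ANOVA. A one-way ANOVA between arms has no sphericity assumption, so there is nothing to adjust. An analyst must guess what was meant.

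The remedy also does not match its trigger. Any one of three failures starts the fallback, but the corrections address only one of them.

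Finally, an ANOVA with two alternative corrections and a GEE model are all to be performed, followed by t or Mann-Whitney tests. If they disagree, nothing says which is reported. At stake is the credibility of the opioid and pain trajectories, the first two secondary endpoints listed. Their p-values could be picked from several analyses or, under one literal reading, be much too small.

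**Working it through.** The plan states no figure that depends on this choice, so there is nothing to reproduce. The check has four parts.

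**1. Trigger against remedy.**

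| Failure that starts the fallback | Addressed by Greenhouse-Geisser / Huynh-Feldt? |
|---|---|
| Non-normality | No |
| Unequal variance | No |
| Non-sphericity | Yes, but only in a repeated-measures ANOVA |

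**2. Will the fallback run?** Sphericity requires all between-timepoint differences to have equal variance. For cumulative opioid use, the difference from 0.5 h to 2 h is 1.5 h of use, and from 0.5 h to 48 h it is 47.5 h of use. As an illustration, assume that use in separate periods is independent with variance proportional to length. The two variances then differ by a factor of 47.5/1.5 ≈ 32. Normality is doubtful as well. The PCIA pump has no background infusion and delivers 4 ml × 1.25 μg/ml = 5 μg per bolus (Anesthesia management and postoperative analgesia). The pilot 24 h mean with TPVB was 25.7 μg (Sample size calculation), which is 25.7/5 ≈ 5 boluses, so early readings take only a few values. The NRS is an 11-point bounded scale (Participants). The fallback is in practice the operative plan.

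**3. Size under different readings.** Inputs from the Protocol article: 83 per arm, 6 timepoints, two-sided 0.05. Assumptions: normal data, no true difference, exchangeable within-patient correlation ρ of 0 to 0.7 (the article gives none). If all readings are pooled as independent, the variance of the arm difference is understated by 1 + 5ρ, and type I error ≈ 2 × [1 − Φ(1.96/√(1 + 5ρ))]:

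- ρ = 0.3: factor 2.5, error 0.215
- ρ = 0.5: factor 3.5, error 0.295
- ρ = 0.7: factor 4.5, error 0.356

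A simulation of 3000 null trials per correlation (simulation error about ±0.008 near 0.05) gives these rejection rates:

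| Analysis | ρ = 0 | 0.3 | 0.5 | 0.7 |
|---|---|---|---|---|
| One-way ANOVA, readings pooled | 0.057 | 0.209 | 0.308 | 0.363 |
| Mann-Whitney, readings pooled | 0.057 | 0.208 | 0.300 | 0.355 |
| Mann-Whitney at one timepoint | 0.056 | 0.049 | 0.048 | 0.046 |
| Repeated-measures ANOVA, between-arm F | 0.058 | 0.046 | 0.053 | 0.047 |
| GEE-type robust test of arm | 0.061 | 0.049 | 0.057 | 0.053 |

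Only the pooled analyses lose their level.

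**4. Six tests by timepoint.** With independent tests, the chance of at least one false positive is 1 − 0.95^6 = 0.265. Simulated with six unadjusted Mann-Whitney tests, it is 0.235, 0.220 and 0.166 at ρ = 0.3, 0.5 and 0.7. This is multiplicity within one series. It does not mean that each test mishandles correlation.

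**The case against.** The strongest defence is that one-way ANOVA is a slip of terminology. The paragraph begins with repeated-measures ANOVA, tests sphericity by Mauchly's test and then applies the two standard corrections. That is the usual sequence for a corrected repeated-measures ANOVA. GEE, named in the same sentence, is built for correlated readings. This is plausible, and it defeats three stronger readings that a reader might infer:

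- **That the fallback ignores within-patient correlation.** It does not: GEE is part of it, and the corrections imply a repeated-measures model.
- **That type I error will be 21–36%.** This needs every patient-timepoint to be pooled as independent, which the article nowhere states. A two-arm one-way ANOVA at a single timepoint is simply the t test and keeps its level.
- **That the Mann-Whitney tests are invalid.** The article assigns them to comparison between arms, opposite the independent-sample t test. At one timepoint the arms are different patients, and the simulated level is 0.046–0.056. The 0.265 figure is the value for six independent tests and concerns multiplicity.

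It can also be said that an analysis plan not shown may supply the model details. That holds for matters such as covariance structure, which are no finding here. It does not cover a method that the article itself names wrongly.

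Three defects survive even the charitable reading. The corrections do not address non-normality or unequal variance. No analysis is named as decisive between ANOVA and GEE. Dependence across timepoints is no reason to choose Mann-Whitney, which does not model it and gives no inference on arm by time.

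**Conclusion.** The point stands as a defect of specification and precedence. As worded, the fallback cannot be carried out: the corrections do not belong to the named test and cover one of its three triggers. It is very likely to be needed, on the reasoning about cumulative use and the bounded, discrete NRS. Running ANOVA as well as GEE without precedence leaves the reported result open to choice after the data are seen.

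No single error rate follows from the text. The 21–36% is conditional on a pooled reading that the plan does not state and on assumed exchangeable correlations of 0.3–0.7. Analyses that respect the correlation stay near 5%. For unadjusted by-timepoint tests, the family-wise error within one six-timepoint series is about 17–24% at the same correlations.

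Only secondary endpoints are touched. The primary non-inferiority decision rests on separate 24 h comparisons and is unaffected.

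**What to change.** Rewrite the paragraph in Statistical analysis, Secondary endpoint, before the database is locked and the allocation revealed:

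- Delete the one-way ANOVA.
- For each repeated outcome, make one model decisive whatever the assumption tests show: GEE with robust standard errors, already named in the plan, or a linear mixed model. Include arm, time and arm × time, and report the arm difference with 95% CI at each timepoint.
- Keep the t or Mann-Whitney tests by timepoint as supportive only, with a multiplicity adjustment or labelled exploratory. Choose between them on distribution and drop the reference to dependence across timepoints.
- Keep the endpoints as defined. Replacing cumulative totals by use per interval would change the endpoint. Requiring a significant arm × time test before any timepoint comparison would block a constant arm difference, which produces no interaction.

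The cost is a few sentences and a few lines of code. The models are available in the SPSS package that the article names. No new data are needed, and the sample size does not change.

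### The non-inferiority rule gives the planned per-protocol analysis no role, so non-inferiority could be claimed when the per-protocol limit crosses the margin

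*Protocol article*

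**What the plan says.** Three parts of the protocol article bear on this.

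- **Analysis sets** (Statistical analysis, last paragraph under Secondary endpoint). "Outcome analyses will be performed in the intention-to-treat (ITT) population", defined as patients kept in their randomized group who "received at least part of study intervention". The next sentence adds the second set: "A per-protocol (PP) analysis will be also performed for the primary endpoint".
- **Decision rule** (Primary endpoint, Non-inferiority). For opioid consumption: "If the effect size upper limit of the one-side 95% CI is smaller than 5 in cumulative 24 h opioid consumption", then "we will conclude that ESPB is non-inferiority to TPVB". For pain: "when average pain NRS scores at 24 h after surgery is smaller than 1, ESPB group will be also considered non-inferiority". Neither sentence names an analysis set.
- **Expected failures** (Sample size calculation). The required 77 per group is raised to 83 for 5% dropout and 3% technique failure. The pilot 24 h sufentanil means given there are 25.7 μg with TPVB and 35 μg without a block.

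**The concern.** The decision rule is unconditional, the general statement on outcome analyses names ITT, and PP is added without a stated consequence. A team that follows the text could obtain an ITT limit below 5 μg and a PP limit above 5 μg, and still declare non-inferiority.

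This matters more in a non-inferiority trial than in a superiority trial. The ITT set keeps a patient whose block was given but failed. If such patients occur about equally in both arms and respond as if unblocked, they make the arms look more alike, and a true loss of efficacy with ESPB is partly hidden. A positive non-inferiority result also opens the superiority tests described under Superiority, so a doubtful claim would carry forward.

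**Working it through.** **Inputs.** From the article: margin 5 μg, one-sided 95% limit, TPVB mean 25.7 μg, no-block mean 35 μg, technique failure 3%, dropout 5%, 83 per arm, NRS margin 1 and SD 2.5.

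Assumed: a failed block has mean 35 μg in either arm, every failure stays in ITT, PP is ITT without the failures, and the SD is common to both arms. Patients analysed per arm: 83 × 0.95 = 78.9, taken as 79.

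**The plan's own figure.** The article does not state the SD behind 77 per group. Solving for it at one-sided 0.05 and 90% power gives SD = 5 × √(77/2) / (1.645 + 1.282) = 10.6 μg. The root mean square of the two pilot SDs, √((2.0² + 14.0²)/2) = 10.0, gives 69 per group, so 77 is not reproduced from the stated inputs. I use 10.6 and show 10 and 14 as a range.

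**Equal failures, 3% in each arm.** Put the true loss among successful blocks at the margin: ESPB 30.7, TPVB 25.7.

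- ITT difference = 5 × (1 − 0.03) = 4.85 μg. The 35 μg cancels because it enters both arms equally.
- SE = 10.6 × √(2/79) = 1.687 μg.
- Probability of an ITT claim = Φ((5 − 4.85)/1.687 − 1.645) = Φ(−1.556) = 6.0%.
- Range: 6.1% at SD 10 (rounded up from 6.05%) and 5.7% at SD 14.
- NRS: the difference shrinks from 1 to 0.97, SE = 2.5 × √(2/79) = 0.398, and the probability is 5.8%.

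**Unequal failures, 6% in one arm only, SD 10.6.**

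- ESPB only: 0.94 × 30.7 + 0.06 × 35 − 25.7 = 5.26 μg. Probability of a claim 3.6%.
- TPVB only: 30.7 − (0.94 × 25.7 + 0.06 × 35) = 4.44 μg. Probability of a claim 9.4%.

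**Requiring both sets.** Simulation at 3% failures in each arm, SD 10.6 and 79 per arm, with Welch limits:

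| True loss among successful blocks | ITT only | ITT and PP |
|---|---|---|
| 5 μg (claim is false) | about 6% | about 4.5% |
| 0 μg (claim is true) | about 90% | about 88% |

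PP alone gives about 5% in the first row. The PP set would hold about 79 × 0.97 = 76.6 per arm, close to the 77 that the article requires.

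**The case against.** **The full protocol may settle this.** The article is a condensed text, and the PP definition and the ranking of the sets often stand elsewhere. That is right for the definition of PP, and its absence here is no finding. It is weaker for the decision rule, which the article states in full and without a condition.

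**Tempting stronger readings.** A reader might infer that the claim rests on ITT alone. The article does not say so: a PP analysis of the primary endpoint is prespecified, and the rule names neither set. A reader might also infer that ITT always favours a false claim. It does not. With failures only in the ESPB arm, the ITT comparison is the stricter one (3.6%).

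**The excess depends on the target.** At 3% failures the ITT difference is 4.85 μg, which is inside the margin. For the ITT effect itself the test keeps its 5% level. The 6% is an error rate only with respect to the effect among successful blocks. This objection stands and limits the point.

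**Even 3% may overstate the dilution.** Patients who receive no part of the intervention leave the ITT set, difficult anatomy is excluded beforehand, and a failed block may still give some relief. Nor would a higher failure rate be supported: adding the 5% dropout to reach 8% would count patients already removed from the 79.

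**PP is not clean either.** It drops patients after randomization. That is a reason to require both sets, not to replace ITT with PP.

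**Conclusion.** The point holds in a limited form. The article plans both analyses but gives PP no part in the non-inferiority decision, so a claim could stand against a PP limit above the margin.

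At the planned 3% failure rate, split equally, the cost is about one percentage point: 6% against 5% for the opioid endpoint, measured against the effect among successful blocks. The size rests on failed blocks behaving like no block, on the assumed SD and on the equal split. With 6% failures in one arm only, it runs from 3.6% (ESPB) to 9.4% (TPVB). The split cannot be known in advance.

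These are figures for one endpoint at a time. They are not the error rate of the trial's overall claim, which also depends on the separate rule that either endpoint suffices. The documents do not support calling this a serious inflation of error. It is a cheap improvement of modest size.

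**What to change.** Add one sentence to the Non-inferiority paragraph: an endpoint is declared non-inferior only if the upper confidence limit of its between-group difference is below its margin in both the ITT and the PP analysis; if the two disagree, non-inferiority is not claimed for that endpoint.

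Both analyses are already planned and no new data are needed. The rule should be fixed before the database is locked and the allocation is revealed. The price is about 2 points of power for the opioid endpoint at 3% failures (about 90% to 88%, under the assumptions above).
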